## Abstract

**Background:** A systematic review of observational studies indicated that eye protection may be an effective measure to prevent SARS-CoV-2 infections. Randomized trials are needed to assess whether the observed associations are caused by protection of the eye or confounding factors such as other systematic differences between users and non-users of eye protection, co-interventions, or changes in COVID-19 incidence when comparisons were done over time.

**Methods:** Pragmatic, virtual, parallel group, 1:1 randomized, superiority trial. We will recruit and randomize participants via an online portal. The trial will be fully remote and virtual without any personal interaction between investigators and participants. All members of the public are eligible who confirm that they are at least 18 years of age, do not regularly wear glasses, have not contracted COVID-19 since December 15th 2021, and are willing to be randomized to wear, or not wear glasses in public when close to other people, for a 2-week period. Persons who are dependent on visual aids but typically use contact lenses are eligible. The participants will be randomized (1:1) to wear glasses (sunglasses or other types of glasses) in public spaces when close to others (public transport, shopping centers etc.), or to the control group. The control group will be asked not to wear glasses in public spaces when close to others. The primary outcome is positive test for COVID-19. We aim to include about 25,000 participants to have a statistical power of 80% to detect a relative risk reduction of 25% for the primary outcome.

**Discussion:** Many have easy access to sunglasses or other glasses. Wearing glasses may provide eye protection and repurposing sunglasses for infection control could be a simple, readily available, environmentally friendly, safe, and sustainable infection prevention measure.

**Trial registration:** NCT05217797 (Clinicaltrials.gov)

## Keywords

COVID-19; non-pharmaceutical intervention; prevention; glasses; pragmatic trial; randomized trial

# Introduction

## Background and rationale

The potential effectiveness of eye protective gear for infection control was pointed out over 100 years ago [1], but this simple intervention has received limited attention during the ongoing pandemic, except as part of Personal Protective Equipment (PPE) for health care workers.

A recent systematic review of studies estimating the impact of eye protection on transmission of SARS-CoV-2 identified 5 observational studies: 1 case-control study, 1 retrospective cohort study, and 3 before-after comparisons [2]. All were conducted among health workers in various settings. With one exception, all studies reported substantial associations between use of eye protection and reduced infection risk, with odds ratios ranging from 0.04 (95% CI 0.00 to 0.69) to 0.6 (0.44 to 0.81). The systematic review authors also identified three cross sectional studies examining the use of glasses in the community, all of which found a substantially lower proportions of people wearing glasses among COVID-19 patients compared to the corresponding proportion for the public in general. A case-control study from Norway, not included in the systematic review, also reported a substantially lower proportion of wearers of eyeglasses among the COVID-19 patients than in the control group, though the difference was reduced and not statistically significant ( $p>0.05$ ) after multivariate adjustment [3].

In summary, the current best evidence indicates that eye protection may be an effective measure for reducing transmission risk, but randomized trials are needed to assess whether the observed associations are caused by protection of the eye or confounding factors such as other systematic differences between users and non-users of eye protection, co-interventions, or changes in COVID-19 incidence when comparison were done over time.

Many have easy access to sunglasses, and it requires little effort to use them in everyday life - after all, some of them are worn just for fashion. Repurposing sunglasses for infection control could be a simple, readily available, environmentally friendly, safe, and sustainable infection prevention measure. Those who regularly use contact lenses could forego using lenses for infection control reasons and wear the eyeglasses they typically have, instead. Again, this could be a very simple measure to prevent infections. We therefore plan to carry out a randomized trial in the community, to assess whether wearing glasses reduces the risk of SARS-CoV-2 infection.

## Objectives

Our objective is to assess whether wearing glasses has an impact on the risk of SARS-CoV-2 infection.

## Trial design

Pragmatic, parallel group, 1:1 randomized superiority trial.

## Methods: Participants, interventions and outcomes

### Study setting

Community. We will recruit participants via an online portal that will be distributed as widely as possible to the Norwegian public. The trial will be fully remote and virtual without any personal interaction between investigators and participants.

NOTE: A similar study is about to be implemented in Denmark. We are closely collaborating with colleagues in other countries to ensure that our protocols are as similar as possible, so facilitate synthesis of findings.

### Eligibility criteria

All members of the public can take part as long as they confirm that they

1. are at least 18 years of age
2. do not regularly wear glasses
3. own or can borrow glasses that they can use (e.g. sun-glasses)
4. have not contracted COVID-19 since December 15th 2021.
5. do not have COVID-19 symptoms
6. are willing to be randomized to wear, or not wear glasses outside their home when close to others for a 2-week period.
7. provide informed consent

Persons who are dependent on visual aids but typically use contact lenses are eligible.

### Who will take informed consent?

Informed, electronically signed consent (MinID or BankID) will be collected on the same web-page where people can sign up to participate and consent to being randomized to the intervention or control group. Participants will also consent to the collection and use of information from questionnaires and national registers.

### Recruitment

We will promote the trial through available media outlets, and invite the public to learn more about the trial on a web-page hosted by the Norwegian Institute of Public Health. The page will include a link to the Nettskjema-platform, where those who wish to participate can receive more information and sign the consent form.

## Interventions

### Explanation for the choice of comparators

This study aims to determine the impact of wearing glasses, in real life circumstances. The intervention is to wear sunglasses or other types of glasses when close to other people outside their home (on public transport, in shopping centres etc.). Consequently, the control group will be encouraged not to wear glasses close to other people outside their home.

### Intervention description

The intervention group will be asked to wear sunglasses (or other types of glasses) when close to others outside their home, e.g. on public transport, in shopping centres etc.

### Criteria for discontinuing or modifying allocated interventions

None. The intervention period is only 14 days for each participant, and we do not plan to define specific criteria for discontinuing or modifying allocated interventions.

### Strategies to improve adherence to interventions

None. We do not plan to maintain any form of contact with the participants between trial enrollment and data collection, 3 days after the 2-week trial period.

### Relevant concomitant care permitted or prohibited during the trial

We will not give any advice about concomitant care or interventions.

### Outcomes

Day 1 of trial period is the first day the individual participates in the trial. The intervention group will be asked to wear glasses until day 14. Three days later (day 17), the participants will complete an online questionnaire.

The primary outcome is

- positive COVID-19 test result registered in public registry (from day 3 to day 17; MSIS database).

Secondary outcomes are

- health care use for respiratory symptoms (from day 3 to day 28; KPR and NPR databases)
- health care use for injuries (from day 1 to day 21; KPR and NPR databases)
- health care use (all causes) from day 1 to day 21 (data source: KPR and NPR databases)
- any positive COVID-19 test result (from day 1 to day 17; self report)
- respiratory symptoms from day 1 to day 17 (self report)
- health care use for respiratory symptoms (from day 1 to day 17; self report)
- health care use for injuries (from day 1 to day 17; self report)
- health care use (all causes) (from day 1 to day 17; self report)

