### Participant timeline

Participants will be enrolled continuously during the winter/spring of 2022. The intervention period for each participant is 14 days.

Table 1: Participant timeline

|                                                | Enrolment/
Allocation | Post-
allocation
follow-up
questionnaire | Registry
data |
|------------------------------------------------|--------------------------|---------------------------------------------------|------------------|
|                                                | Day 1                    | Day 17                                            | Day
17/21/28  |
| Recruitment & Baseline assessment   |                          |                                                   |                  |
| Eligibility criteria                           | X                        |                                                   |                  |
| Informed consent                               | X                        |                                                   |                  |
| Randomization                           |                          |                                                   |                  |
| Interventional: Advise to wear glasses         | X                        |                                                   |                  |
| Control: Routine life                          | X                        |                                                   |                  |
| Outcome measures                        |                          |                                                   |                  |
| Positive COVID-19 test result                  |                          | X                                                 | X                |
| Symptoms of respiratory symptoms               |                          | X                                                 |                  |
| Need for medical care (all-cause)              |                          | X                                                 | X                |
| Need for medical care (related to respiratory) |                          | X                                                 | X                |

|                                                                                                                  |  |   |    |

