|------------------------------------------------------------------------------------------------------------------|--|---|----|
| symptoms)                                                                                                        |  |   |    |
| Need for medical care (due to injuries)                                                                          |  | X | X  |
| Participant characteristics (registers)                                                                   |  |   |    |
| Age, gender, vaccination status, notified test results (COVID-19), registered medical care/admission to hospital |  |   | X* |

\* Data on vaccination status and notified COVID-19 test results, will also be collected for the pre-study period

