### Sample size

Assuming no loss to follow-up and that wearing of glasses leads to a relative risk reduction of 25% for the primary outcome, we will need around 22,000 participants self-reporting on the primary outcome to detect a statistically significant effect ( $p < 0.05$ ) with 80% power. This is based on an expected event rate for the primary outcome in the control group (real life) of 2% (14-day incidence of 2000/100,000).

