#### **Methods in analysis to handle protocol non-adherence and any statistical methods to handle missing data**

We will include all data collected, and it will be analyzed by the intention to treat principle. We do not plan to use any methods for handling missing data.

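### The primary outcome counts any registered positive from day 3 to day 17 and does not require it to be a new infection, although the registry data that would show this are collected

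*Protocol*

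**What the plan says.** The Protocol's objective is the effect of wearing glasses on the risk of SARS-CoV-2 infection (Objectives). The primary outcome is a "positive COVID-19 test result registered in public registry (from day 3 to day 17; MSIS database") (Outcomes).

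- **Time frame.** "Day 1 of trial period is the first day the individual participates in the trial", and "The intervention group will be asked to wear glasses until day 14". Participant timeline adds: "The intervention period for each participant is 14 days". The self-reported version of the outcome starts on day 1 instead of day 3.
- **Entry.** Participants confirm that they "have not contracted COVID-19 since December 15 th 2021" and that they have no COVID-19 symptoms (Eligibility criteria). No baseline test is described.
- **Registry data before entry.** The footnote to Table 1 says: "Data on vaccination status and notified COVID-19 test results, will also be collected for the pre-study period". The only stated analysis by earlier infection is an optional subgroup (Methods for additional analyses).
- **Analysis set.** "We will include all data collected, and it will be analyzed by the intention to treat principle" (section on non-adherence and missing data).
- **Sample size.** About 22,000 participants for 80% power and a 25% relative reduction. "This is based on an expected event rate for the primary outcome in the control group (real life) of 2% (14-day incidence of 2000/100,000").

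**The concern.** The objective is about acquiring infection, but the endpoint is about having a positive registered. The two differ for a person whose infection was registered before randomisation, or on day 1 or 2, and who has another positive registered on day 3 or later. Read literally, that person has a primary event. The glasses could not have prevented an infection that was already registered before entry, and the protocol itself leaves days 1-2 out of the primary outcome.

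At stake is some dilution of the primary relative risk and some power. The sample size has little room for it, since 22,000 gives barely more than the planned 80%. An event rule settled only after the data have been seen would also be open to the charge of being post hoc.

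**Working it through.** **1. The plan's own figure.** Inputs from Sample size: control risk 2%, relative reduction 25% (so 1.5% with glasses), p < 0.05 (taken as two-sided), power 80%, no loss to follow-up, 1:1 allocation. With p̄ = 0.0175:

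n per arm = {1.96·√[2·p̄(1−p̄)] + 0.842·√[0.02·0.98 + 0.015·0.985]}² / 0.005² = 10,795, or 21,590 in total.

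This agrees with the stated figure of around 22,000. At 11,000 per arm the same formula gives 80.7% power; at 12,500 per arm (the Abstract's target of about 25,000) it gives 85.4%.

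**2. Who counts as an event, as written.**

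| First registered positive | Further positive on days 3-17 | Event as written | Event if a first positive is required |
|---|---|---|---|
| 15 Dec 2021 to day before randomisation | Yes | Yes | No |
| Day 1 or 2 | Yes | Yes | No |
| Day 3 to 17 | Either | Yes | Yes |

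The entry criteria should keep most of the first row out, but only by self-report. They cannot keep the second row out.

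**3. Size, by assumption.** Let r be the share of control events that are such repeats. Glasses do not affect them, so

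observed RR = r + 0.75(1 − r) = 1 − 0.25(1 − r).

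With the control risk held at 2% and 11,000 per arm (220 expected control events):

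| r (assumed) | Control events that are repeats | RR | Risk with glasses | Power |
|---|---|---|---|---|
| 0 | 0 | 0.750 | 1.500% | 80.7% |
| 2% | 4.4 | 0.755 | 1.510% | 79.0% |
| 5% | 11 | 0.7625 | 1.525% | 76.3% |

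A first-positive rule restores RR = 0.75 but also removes those events. The control risk becomes 2%·(1 − r) = 1.96% or 1.90%, and power 79.9% or 78.7%. The rule therefore recovers the estimate fully and the power in part.

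**4. The window, checked separately.** Days 3 to 17 inclusive are 17 − 3 + 1 = 15 days; exposure on days 1 to 14 is 14 days. The start is offset by 2 days and the end by 3. Assume a fixed lag of L days from infection to registered positive and constant incidence. A window day d is then informative if 1 ≤ d − L ≤ 14. With k informative days out of W, RR = 1 − 0.25·k/W. The 2% is treated as a 14-day rate, so the control risk over 15 days is 2%·15/14 = 2.14%. Power at 11,000 per arm:

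| Lag L (assumed) | Days 3-17: k of 15 | Power | Days 4-17: k of 14 | Power |
|---|---|---|---|---|
| 1 | 13 | 71.1% | 12 | 67.0% |
| 2 | 14 | 77.7% | 13 | 74.3% |
| 3 | 14 | 77.7% | 14 | 80.7% |
| 4 | 13 | 71.1% | 13 | 74.3% |
| 5 | 12 | 63.7% | 12 | 67.0% |

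No lag makes all 15 days informative. Starting on day 4 gains about 3 points at lags of 3 to 5 days and loses 3 to 4 points at lags of 1 or 2 days. At lags 1 and 2 the uninformative days come after exposure ends, not before randomisation.

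**The case against.** Several counter-arguments have weight.

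- **Safeguards exist.** Participants confirm no COVID-19 since 15 December 2021 and no symptoms, and days 1-2 are already left out of the primary outcome. This stands, and it keeps the number of repeats down. It does not exclude misreported earlier infection, or a positive on day 1 or 2 followed by another in the window.
- **The number may be nil.** The documents do not say whether the registry lists repeat positives separately. This stands. If it does not, the first-positive rule changes nothing and costs nothing.
- **Duplicate records are analysis-plan detail.** This holds in part. De-duplication code can wait for the analysis plan, but whether the primary event must be a first positive is part of the endpoint's definition. The sentence about including all data comes from the section on missing data and does not itself make repeats events; the outcome wording does.
- **Removing randomised participants would depart from the stated intention-to-treat analysis.** This stands, so the fix keeps everyone in.

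A reader might also infer from the 15-day window that infections incubating at randomisation cost the trial up to 20 points of power, and that the window should therefore start on day 4. The documents do not support this. The large losses come from assumed lags of 4 or 5 days, and a day-4 start recovers only about 3 points of them. The 3-day end lag is inferred from the questionnaire date; no section states it as a time from infection to test. At 12,500 per arm and a 3-day lag, the current window still gives 82.7%.

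**Conclusion.** The concern holds, at minor severity. As written, the primary endpoint admits repeat positives of infections registered before randomisation or on days 1-2, while the data that would identify them are requested and left unused in the definition.

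The effect is dilution. Provided that retesting does not depend on the arm, such events are balanced in expectation, the relative risk moves toward 1, and the type I error is not inflated. A reader might infer a bias in favour of glasses; nothing in the documents supports that. The loss of about 2 to 4 points of power rests on assumed repeat shares of 2% and 5%, a true 25% reduction, a 2% control risk and 11,000 per arm.

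The mismatch between window and exposure is real, but it does not justify replacing the primary window, because the better start day turns on an unstated lag. Requiring a first positive does not remove infections that were incubating at randomisation and first detected from day 3; only the later-start sensitivity analyses address those.

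**What to change.** 1. Define the primary event as the participant's first MSIS-registered positive since 15 December 2021, by test date, falling on days 3 to 17.
2. Keep every randomised participant in the intention-to-treat analysis. Count those whose first positive since 15 December 2021 came before the window (pre-study or days 1-2) as non-events.
3. Prespecify as sensitivity analyses: (a) the any-positive count on days 3 to 17; (b) an analysis excluding participants with a registered positive from 15 December 2021 to the day before randomisation, which uses only information fixed before allocation; (c) windows of days 4 to 17 and later starts.
4. State the reason for starting on day 3, and fix all of this before allocation is revealed to the analysts.

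The cost is a change of outcome wording and a few lines of code on data already requested. A few events leave the numerator. A true reinfection in someone with a positive earlier in the period would also be lost, but sensitivity analysis (a) still counts it.

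### Three self-reported infection outcomes start on day 1, not day 3 as in the registry, so they take in day 1-2 events that largely predate allocation (minor)

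*Protocol*

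**What the plan says.** All the windows are in the protocol's Outcomes section, which fixes the clock: "Day 1 of trial period is the first day the individual participates in the trial". Table 1 (Participant timeline) places both enrolment and allocation on that day.

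- Primary outcome, from the registry: "positive COVID-19 test result registered in public registry (from day 3 to day 17; MSIS database".
- Respiratory care, from the registry: "health care use for respiratory symptoms (from day 3 to day 28; KPR and NPR databases".
- Injuries, from the registry: "health care use for injuries (from day 1 to day 21; KPR and NPR databases". All-cause care from the registry has the same window.
- Self-reported infection outcomes: "any positive COVID-19 test result (from day 1 to day 17; self report", "respiratory symptoms from day 1 to day 17 (self report" and "health care use for respiratory symptoms (from day 1 to day 17; self report". Self-reported injuries and all-cause care also cover days 1 to 17.

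Under Eligibility criteria, participants confirm that they "do not have COVID-19 symptoms" and that they have not had COVID-19 since mid-December 2021. No test at entry is listed. The protocol gives no reason for the different start days.

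**The concern.** Among the registry outcomes, the later start applies only to the two that concern infection; injuries and all-cause care start on day 1. That pattern fits an intention to leave out infections acquired before allocation. The self-report list makes no such distinction. A participant who joins while incubating and tests positive on day 2 is an event in the self-reported outcome but not in the primary outcome.

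Two things are at stake. First, the three self-reported outcomes count events that glasses could hardly have prevented, which moves the relative risk towards 1. Second, the self-reported positive test, the closest analogue of the primary outcome, covers different days from it.

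**Working it through.** **Windows side by side**

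| Outcome | Registry | Self-report | Start differs | End differs |
|---|---|---|---|---|
| Positive test | 3-17 | 1-17 | yes | no |
| Respiratory care | 3-28 | 1-17 | yes | yes |
| Respiratory symptoms | none | 1-17 | - | - |
| Injuries | 1-21 | 1-17 | no | yes |
| All-cause care | 1-21 | 1-17 | no | yes |

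**Inputs from the protocol's Sample size section:** control risk 2%, relative risk 0.75 (so 2.0% against 1.5%), alpha 0.05, power 80%, no loss to follow-up, about 22,000 participants. Allocation is 1:1. A two-sided test is assumed, because the protocol does not state sidedness.

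**Step 1: reproduce the stated size.** For two proportions with mean p̄ and q̄ = 1 − p̄:

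n per arm = [1.96·√(2p̄q̄) + 0.8416·√(p₁q₁ + p₂q₂)]² / (p₁ − p₂)²

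With p₁ = 0.020 and p₂ = 0.015 this gives 10,795 per arm, or 21,590 in total (22,384 with continuity correction). Both agree with about 22,000. A one-sided test gives 17,008 and does not.

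**Step 2: dilution.** Assumptions that are not in the protocol: a constant daily event rate, the full effect from day 3 (15 days, days 3 to 17), and no effect on days 1-2. If k days' worth of unaffected events is added:

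observed RR = (15 × 0.75 + k) / (15 + k)

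- k = 2, the day-1 start as written: 13.25/17 = 0.779. Early events are 2/17 = 12% of control events.
- k = 1, as if the entry screen removed half of the early events: 12.25/16 = 0.766. Early events are 1/16, about 6%.

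**Step 3: what this means in numbers.** Take 11,000 per arm, full response, and 2% spread evenly over days 3-17, so the daily rate is 0.02/15 = 0.133%.

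- Day-3 start: 220 against 165 events (2.00% against 1.50%).
- Day-1 start: 2 × 0.133% × 11,000 ≈ 29 further events in each arm, so about 249 against 194 (2.27% against 1.77%).

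The absolute difference stays at 0.5 percentage points. Only the ratio and its precision change.

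Power = Φ{[|p₁ − p₂|·√n − 1.96·√(2p̄q̄)] / √(p₁q₁ + p₂q₂)}

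| Assumed rate | Day-3 start | k = 1 | k = 2 |
|---|---|---|---|
| 2% over days 3-17 | 80.7% | 77.9% | 75.1% |
| 2%/14 per day | 83.4% | 80.7% | 78.0% |

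In the first row with k = 2, 80% power would need 24,814 respondents.

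**The case against.** The strongest reply is that this is a choice, not a contradiction. All five self-reported outcomes share one window because they come from one questionnaire on day 17, with no contact in between. The time since joining is a natural recall period. The protocol never says that day 3 was chosen to exclude infections acquired before allocation; that is inferred from the pattern of windows. This stands, and it is one reason why the point is minor.

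The figures also lean high. The entry criteria should remove some early events, though not presymptomatic or asymptomatic infections. The effect will not begin sharply on day 3 either: some later positives also reflect exposure before allocation, so a day-3 start reduces the dilution without removing it. Dating events asks unblinded participants to make a recall judgement that a day-1 start avoids.

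A reader might infer more than the documents support:

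- *That the trial's main result or its size is compromised.* The Sample size section does describe its participants as self-reporting the primary outcome, but the Outcomes section defines that outcome from the registry with a day-3 start. The protocol claims no power for the three outcomes at issue, so the percentages above only illustrate scale.
- *That the day-1 start favours one arm.* Infections acquired before allocation are balanced by randomization in expectation. The result is attenuation only.
- *That every self-reported outcome fails to match a registry twin because of its start day.* Respiratory symptoms have no twin; Table 1 marks them for the questionnaire only. The respiratory-care pair differs far more at the end (11 days) than at the start (2 days).
- *That self-report was meant as a check on the registry and can no longer serve.* The protocol gives it no such role. Non-response, and counting any positive test rather than registered ones, would separate the two in any case.
- *That early events can never be removed because no dates are collected.* The question list under Plans for assessment and collection of outcomes omits even the test and symptom questions, so it is not the full form. Whether dates are asked cannot be determined.

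**Conclusion.** The point holds as a minor one. As written, three of the eight secondary outcomes include day 1-2 events that allocation on day 1 can hardly affect, and the self-reported positive test has a different window from the primary outcome. The expected consequence is mild dilution: a relative risk of 0.75 would appear as at most about 0.78, given a constant daily rate and no effect on days 1-2, and as about 0.77 if half of those early events are screened out. For the self-reported positive test, under the same assumptions and full response from 22,000, illustrative power falls by about 5 to 6 percentage points (83.4% to 78.0%, or 80.7% to 75.1%). The day-1 start for injuries and all-cause care is not in question.

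**What to change.** In the Outcomes section, start the self-reported positive test, respiratory symptoms and respiratory health care on day 3 and end them on day 17. On the day-17 form, show each participant the calendar dates of their own day 3 and day 17. Ask for the date of the first positive test, of symptom onset and of the first respiratory visit, unless the form already does so. Keep the day 1-17 version of each outcome as a sensitivity analysis, because date recall by unblinded participants is imperfect. Leave injuries and all-cause care starting on day 1.

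This fully aligns the windows of the positive-test pair only. For respiratory care, the registry outcome can also be tabulated for days 3-17 beside its day 3-28 definition, so that the two sources can be compared over the same days.

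The cost is three reworded windows, at most a few date fields on a web form, slightly longer completion, and some error in recalled dates.
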